### Eligibility criteria

2.3.

Patient enrolment and clinical evaluation will be done by a certified neurologist and include the following inclusion and exclusion criteria:

Inclusion criteria:

Active epilepsy (medication for epilepsy and/or had at least one seizure in the past year).Adults (≥18 years).Lithuanian speakers.No intellectual disability.

Exclusion criteria:

Sensory or motor deficit preventing task completion.Epilepsy surgery planned during the project.Active non-paroxysmal comorbid disorder of the central nervous system (e.g., neurodegeneration, multiple sclerosis).Active psychiatric disorder during the past year.Psychoactive substance use (except social alcohol, tobacco and caffeine use).

Patients with temporal lobe epilepsy as well as genetic generalized epilepsy will be enrolled.

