Secondary outcomes will include symptoms of depression (Neurological Disorders Depression Inventory in Epilepsy, NDDI-E) (13, 14), anxiety (General Anxiety Disorder-7, GAD-7) (15) and suicidality (Columbia Suicide Severity Rating Scale, C-SSRS) (16), metacognition (Metacognition Questionnaire-30, MCQ-30) (17, 18), Jacoby’s 3-item Stigma Scale (19), antiseizure drug adverse effects (Liverpool Adverse Events Profile, LAEP) (20, 21), health-related quality of life [the Short Form (36) Health Survey] (22) and subjective evaluation of cognitive functions (*ad hoc* Likert scales 0 to 10). Secondary cognitive outcomes will include reaction speed (Trail Making Tests A and B, Maze Task), working memory (Digit Span Test), verbal fluency (categorical and phonemic naming in 60 s), autobiographical memory (naming of recent personal autobiographical events), delayed verbal story recall as well as 1-week verbal recall to test for accelerated long-term forgetting. An experimental task set to test learning and recall of a hypothetical weekly schedule will also be used (Figure 1). This task was created by the authors and will be explored for applicability in testing for real-world event data, such as memory of where (e.g., in conference room 62B of the office), when (e.g., Monday at 15:30) and for what purpose (e.g., to be present in a business meeting) the participant is hypothetically planning to participate. The task will also include an item about preparatory actions before each activity (e.g., familiarize with material of the meeting in the latter example) and will be scored for each item recalled (maximum of 20 points). Given the exploratory nature of the task, it has not been previously validated and will rely on comparison between early and late intervention groups.

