### Participant recruitment, allocation, and timeline

2.6.

Study participants will be invited to participate in the trial during routine outpatient visits at the epilepsy clinic. They will have either temporal lobe or genetic generalized epilepsy as confirmed by the epileptologist, according to previously collected clinical (e.g., seizure semiology, patient history), instrumental (e.g., electroencephalography, video-electroencephalography), genetic and imaging (e.g., 3T magnetic resonance imaging) data required to substantiate the diagnosis according to guidelines by the International League Against Epilepsy. After acceptance, each new participant will be randomly assigned to either the early intervention group (EIG) or the late intervention group (LIG) at the time of enrolment by using open-source software for minimization (WinPepi) based on sex, epilepsy type and seizure control. The randomization will be done, and participants assigned to one of the groups by the principal investigator. Outcome assessors and data analysts will be blinded to participant status by using concealed patient coding and instructing patients not to discuss their status during examination. The principal investigator, psychologists performing the intervention and participants themselves will not be blinded.

Both the EIG and the LIG will undergo neuropsychological assessment at three time points (Figure 2). The EIG will be tested at baseline, with two follow-ups four and sixteen weeks after the intervention which itself lasts for eight weeks. The LIG will be tested at the same time points while on waitlist. Participants assigned to the LIG will be offered the intervention after the second follow-up. Both groups will receive otherwise routine clinical care (i.e., according to individual needs and best medical practice) at the tertiary epilepsy clinic. Given the non-invasive nature of the CoRE intervention, no adverse effects are expected. Therefore, discontinuation of the intervention is expected to occur only in the case of participant dropout. Patient attrition will be minimized by thoroughly discussing the aims and procedures of the trial before enrolment as well as by accommodating to the patients’ availability and daily schedule for the weekly sessions.

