### Sample size and statistical analysis

2.7.

The target sample size of the study was calculated for a between-group interaction of a two-way repeated measures analysis of variance (ANOVA) with *f* = 0.40, *α* = 0.05, *β* = 0.95, two groups (early and late intervention), three measurement points, and 0.5 correlation between repeated measures. The resulting sample size of *n* = 58 (G*Power 3.1.9.7) was increased by 20% to *n* = 70 to account for dropouts (including the possibility of patient referral to presurgical evaluation if needed according to principles of best medical practice) and corresponded well to the mean sample size and attrition rates in previous trials (5). This sample size is deemed achievable as the trial will be conducted in a large university hospital covering tertiary epilepsy care services for approximately 1.4 million of inhabitants and include a group of PWE composed of patients with both TLE and GGE.

The efficacy of the intervention will be defined as statistically significant improvement on one of the primary outcomes (quality of life or delayed memory), tested with a repeated-measures between-factors analysis of variance (ANOVA) in the EIG as compared to the LIG. For secondary analyses, dynamic changes of other outcome measures will be tested, respectively, by using ANOVA or ANCOVA. The association between demographic and clinical variables with study endpoints will be conducted by means of linear and ordinal regression modeling. Subgroup analyses are planned to be conducted based on sex, education status, professional status, epilepsy type, laterality and lesionality. In case of missing data, multiple imputation will be used in sensitivity analysis.

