Moreover, the assessment we suggest includes testing for mental health status, metacognition and quality of life in addition to objective cognitive performance. The psychosocial status of the patient will be evaluated to adjust for subclinical levels of anxiety and depression as well as to see whether CoRE may improve patient mental health. Moreover, we will also investigate suicidality – this part of the evaluation is rarely done in the clinical setting and is especially important in Lithuania, which has extremely high suicide rates (14). Patients will also complete a metacognition questionnaire – a relatively novel tool in PWE set to assess coping and thinking mechanisms that underlie self-regulation in psychopathology and may help to explain better response to CoRE (17, 18). Finally, patient-oriented outcome measures (i.e., quality of life) will be essential to define the overall impact of the CoRE program (30, 31).

To increase the likelihood of the efficacy of the tested intervention, it will be done by following the S.O.S. toolbox: Strategies (internal and external), Outsourcing (use of physical and digital media) and Social support (education and co-operation) (6, 32). The intervention includes elements of psychoeducation mindfulness, positive psychology and acquires intensity from weekly homework that makes the program a continuous process that is not limited to the sessions themselves. The intervention will combine compensatory and restitution techniques alongside focus on general mental well-being and self-regulation. Because of such a varied inventory within the CoRE program, we expect it to have transfer effects for domains that will not be trained directly (e.g., long-term memory) (28).

Finally, our trial includes a longer follow-up period: while most previous studies had a limited follow-up period of 12 weeks, our timeline will include a follow-up of 16 weeks and provide a better estimate of the maintenance effects of CoRE (5).

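### The only stated arm comparison for suicidality (C-SSRS) is ANOVA or ANCOVA; a mean difference does not show how many patients worsen, and improvers can offset them

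*Protocol article*

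**What the plan says.** The Outcomes section (2.5) of the protocol article includes among the secondary outcomes "suicidality (Columbia Suicide Severity Rating Scale, C-SSRS"). It names the instrument but does not say how it will be scored or which endpoint will be derived from it.

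Section 2.7 then sets the analysis of all outcomes other than the primary ones in a single sentence: "For secondary analyses, dynamic changes of other outcome measures will be tested, respectively, by using ANOVA or ANCOVA". The C-SSRS is not exempted. Regression models appear in the next sentence, for a different purpose: "The association between demographic and clinical variables with study endpoints will be conducted by means of linear and ordinal regression modeling". That relates patient characteristics to endpoints and does not compare the arms.

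Two statements in the Discussion bear on the purpose of the measure. The psychosocial assessments serve in part "to see whether CoRE may improve patient mental health", and assessing suicidality is described as "especially important in Lithuania, which has extremely high suicide rates". On harm, section 2.6 says: "Given the non-invasive nature of the CoRE intervention, no adverse effects are expected".

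**The concern.** A comparison of means answers how far the average score moved. For suicidality a reader mainly wants to know how many patients newly developed or worsened in ideation, how many improved, and whether any suicidal behaviour occurred. A mean difference answers none of these, for two reasons:

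- The same mean difference can come from a few patients with severe new ideation or from many with a slight change.
- Improvement in some patients can offset worsening in others within the same arm. The programme is hoped to improve mental health, so the intervention arm may contain improvers, and that is also where any worsening would need to be seen.

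The article expects no adverse effects and states no other arm comparison of suicidality. A null ANOVA result could therefore be taken as reassurance that it cannot give.

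**Working it through.** **Inputs**

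- Patients per arm: 58 / 2 = 29, from n = 58 in section 2.7, with equal allocation assumed. The 58 reproduces for the between-groups test of a repeated-measures ANOVA: noncentrality = f² × N × m / (1 + (m − 1) × ρ) = 0.16 × 58 × 3 / 2 = 13.92 on 1 and 56 df, which gives power 0.956. It was derived for the primary outcomes; the article gives no figure for the C-SSRS.
- Scale: ideation coded 0 to 5. This is an assumption.
- Counts of patients who change: all invented for illustration, since the article gives no rates. One follow-up is used for simplicity.

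**1. Same mean difference, different patients.** In each pattern everyone starts at 0 and the other arm does not change.

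- Pattern A, two patients go from 0 to 4: mean difference = 2 × 4 / 29 = 0.276. Sum of squares = 2 × 16 − 8² / 29 = 29.79; pooled variance = 29.79 / 56 = 0.532; SE = √(0.532 × 2 / 29) = 0.192; t = 0.276 / 0.192 = 1.44 on 56 df; p = 0.155.
- Pattern B, eight patients go from 0 to 1: mean difference = 8 × 1 / 29 = 0.276. Sum of squares = 8 × 1 − 8² / 29 = 5.79; pooled variance = 5.79 / 56 = 0.103; SE = √(0.103 × 2 / 29) = 0.084; t = 3.27; p = 0.0019.

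The estimate is identical. As counts, the patterns are 2/29 (7%) at a severe level and 8/29 (28%) at a mild one.

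**2. Cancellation.** Each arm starts with four patients at level 2 and 25 at level 0. In one arm all four remit and two others go from 0 to 4. In the other arm nobody changes.

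- Baseline means: 4 × 2 / 29 = 0.276 in both arms, so the baseline difference is 0.
- Follow-up means: 2 × 4 / 29 = 0.276 and 4 × 2 / 29 = 0.276, so the follow-up difference is 0.
- ANOVA on change: mean change = (4 × (−2) + 2 × 4) / 29 = 0 against 0; p = 1.0.
- ANCOVA: follow-up difference minus slope × baseline difference = 0 − slope × 0 = 0; p = 1.0.

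The same data as counts, with Newcombe score intervals for the risk difference:

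| | One arm | Other arm | Difference (95% CI), points | Fisher p |
|---|---|---|---|---|
| New or worsened | 2/29 | 0/29 | 6.9 (−5.8 to 22.0) | 0.49 |
| Improved or remitted | 4/29 | 0/29 | 13.8 (−0.5 to 30.6) | 0.11 |

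Both movements are now visible, although neither is significant.

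**3. What counts can and cannot do at this size**

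- Fisher's test for k/29 against 0/29 gives p = 0.052 at k = 5 and p = 0.023 at k = 6, so significance needs six cases against none.
- With no cases in either arm, the Newcombe interval for the difference is ±11.7 points at 29 per arm and ±9.9 points at 35 per arm (70 / 2).

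**The case against.** The strongest reply is that this belongs to the statistical analysis plan. Section 2.7 covers a long list of outcomes in one general sentence, and nothing in it forbids a table of counts. That is partly right: a separate plan may well add one, and its absence here is not the point. But the sentence does fix a method for every other outcome, and that method suits this one badly.

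Second, the premises are not in the document. The article does not describe C-SSRS scoring. That most patients will score zero is only an inference from the exclusion of "Active psychiatric disorder during the past year", while the Discussion points the other way by mentioning subclinical anxiety and depression and high suicide rates. This stands as a limit. The ordered, yes/no form of the scale is an assumption here. The two worked examples do not depend on the share of zeros.

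Third, improvers can offset worseners in any comparison of means, and the example was built so that they match exactly. Also true. The reason to treat suicidality differently is that a single severe case matters in itself, which is not so for a few points on an anxiety or quality-of-life scale.

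Fourth, counts give no firmer conclusion: in the cancellation example Fisher's test gives p = 0.49 for worsening. This stands, and no gain in power is claimed.

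A reader might go further and infer that ANOVA on sparse scores would produce false positives or badly covering confidence intervals. The document does not support this. Section 2.7 speaks of tests and promises no intervals. In simulations with assumed equal rates of 1–10% in both arms, the ANOVA test rejected in only 0.3–4.9% of trials, so it was nominal or conservative.

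**Conclusion.** The concern holds as a minor point of analysis choice. ANOVA or ANCOVA is the only arm comparison stated for suicidality. Under the usual form of the scale, it cannot show how many patients newly develop or worsen in suicidality, and it can return a difference of 0 with p = 1.0 when two patients have new level-4 ideation and four have remitted.

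This rests on the assumed 0–5 coding, equal arms of 29 and invented counts. The examples show what a mean can hide, not how likely that is in this trial.

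The stakes are limited. The C-SSRS is not among the key secondary outcomes in Table 1 and plays no part in the efficacy definition in section 2.7. The primary results and the sample size are unaffected. Nor should the point be read as saying that suicidality goes unmeasured or that harm is expected: the scale is planned for both arms, and the article gives no sign of an actual risk.

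**What to change.** In section 2.7, make the main arm comparison for the C-SSRS categorical. By arm, at 4 and 16 weeks after the intervention, report the number and percentage of participants with:

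- new or worsened ideation relative to baseline;
- improved or remitted ideation relative to baseline, with both movements shown in a baseline-to-follow-up shift table;
- any suicidal behaviour.

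Give the between-arm risk differences with score or exact 95% confidence intervals, and state that a non-significant result will not be read as absence of harm. Any ANOVA or ANCOVA on the C-SSRS should be supplementary. Reporting improvement as well as worsening keeps the Discussion's question about mental-health benefit in view; counts of worsening alone would hide the remissions.

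The cost is a short addition to 2.7 and one extra table. The data are already planned: section 2.6 assesses the intervention arm at baseline and both follow-ups and says of the control arm "The LIG will be tested at the same time points while on waitlist". No new visits or patients are needed. The price is wide intervals, about ±12 points with no cases at 29 per arm, and no gain in power.

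### Secondary outcomes may be tested by ANOVA or ANCOVA, with neither the outcome's own baseline score nor the minimisation factors fixed as covariates

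*Protocol article*

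**What the plan says.** Section 2.7 (Sample size and statistical analysis) specifies the secondary analysis in one sentence: "dynamic changes of other outcome measures will be tested, respectively, by using ANOVA or ANCOVA". The adverb *respectively* implies that each outcome is matched to a model, but no matching is printed. No covariate is named for the ANCOVA. The primary outcomes have a separate statement: they are "tested with a repeated-measures between-factors analysis of variance (ANOVA) in the EIG as compared to the LIG".

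Baseline scores are planned in both arms. Section 2.6 states: "The EIG will be tested at baseline, with two follow-ups four and sixteen weeks after the intervention". For the waitlist arm it adds: "The LIG will be tested at the same time points while on waitlist". The Discussion confirms that the baseline assessment uses the same kinds of instrument as the follow-ups. Section 2.6 also says that allocation uses software "for minimization (WinPepi) based on sex, epilepsy type and seizure control".

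The only adjustment variables named for the psychosocial assessment are subclinical anxiety and depression, in the Discussion. The Limitations section mentions adjusted analyses in general terms.

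**The concern.** ANOVA and ANCOVA are not interchangeable ways of comparing randomised arms. With the outcome's own baseline score as covariate, ANCOVA is in large samples at least as precise as an ANOVA of the follow-up score or of the change score. Here the baseline score is planned for collection anyway, so listing ANOVA as an alternative gains nothing.

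Three things are at stake. First, real effects on mood, stigma, metacognition and the secondary cognitive tests are more easily missed in a trial of 70. Second, the minimisation factors are not carried into any comparison of arms; to the extent that they predict an outcome, leaving them out makes its standard error too large. Third, an open either/or, with an unnamed covariate on one side, leaves room to choose the model outcome by outcome after seeing results. Section 2.5 lists more than a dozen secondary measures, so the choice recurs often.

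**Working it through.** **Inputs.** From section 2.7: "with *f* = 0.40, *α* = 0.05, *β* = 0.95" and "two groups (early and late intervention), three measurement points, and 0.5 correlation between repeated measures". The value 0.95 is printed as β but makes sense only as power. The calculated total of 58 "was increased by 20% to *n* = 70 to account for dropouts". Assumed here, because the document does not state them: 1:1 allocation (58/2 = 29 per arm), equal variances at all visits, and a true effect of 0.5 SD.

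**The plan's own figure.** For a repeated-measures ANOVA, between factors, with m = 3 visits: λ = f²·N·m / (1 + (m − 1)ρ). At N = 58, λ = 0.16 × 58 × 3 / 2 = 13.92 and power is 0.956. At N = 56, power is 0.9495. So N = 58 is reproduced, and 58 × 1.2 = 69.6, which rounds to 70. This sizing concerns the primary ANOVA. It is used here only as the source of ρ = 0.5 and of 29 per arm.

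**Relative variance of the arm difference, one follow-up**
- ANOVA of the follow-up score: 1
- ANOVA of change: 2(1 − ρ) = 2 × 0.5 = 1
- ANCOVA on own baseline: 1 − ρ² = 1 − 0.25 = 0.75
- Ratio of either ANOVA to ANCOVA: 1/0.75 = 1.33

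**Relative variance, mean of the two follow-ups**
- ANOVA of the mean: (1 + ρ)/2 = 0.75
- ANOVA of the mean minus baseline: 0.75 + 1 − 2 × 0.5 = 0.75
- ANCOVA on own baseline: 0.75 − 0.25 = 0.50
- Ratio: 0.75/0.50 = 1.5

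**Sensitivity to the correlation, one follow-up**

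| ρ | Follow-up ANOVA ÷ ANCOVA | Change ANOVA ÷ ANCOVA |
|---|---|---|
| 0.3 | 1.10 | 1.54 |
| 0.5 | 1.33 | 1.33 |
| 0.7 | 1.96 | 1.18 |
| 0.8 | 2.78 | 1.11 |

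ANCOVA is never the less precise option, and neither form of ANOVA is uniformly the better of the two.

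**Power, 0.5 SD, 29 per arm, one follow-up, ρ = 0.5 (noncentral t, two-sided 5%)**
- ANOVA, follow-up or change: noncentrality 0.5/√(2/29) = 1.90; power 0.465
- ANCOVA: noncentrality 0.5/√(0.75 × 2/29) = 2.20; power 0.579

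**Type I error if the smaller p-value were reported.** At ρ = 0.5, the ANOVA estimate (follow-up or change) and the ANCOVA estimate have correlation √0.75 = 0.866. The chance that at least one of two such statistics passes the two-sided 5% limit is 0.073. Simulation with 29 per arm gives 0.074. If both forms of ANOVA and the ANCOVA were all open, it is about 0.097.

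**The case against.** The strongest reply is that this is a condensed article. Covariates and outcome-by-outcome models are commonly left to an analysis plan, which is not shown, and the absence of that detail is no fault. That stands. The point therefore rests on what is printed: the article does specify the secondary analysis, and it specifies it as a choice between two non-equivalent models.

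A reader might infer more than the text supports, in four ways:

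- **That baseline would be ignored under ANOVA.** The sentence is about changes over time, so an ANOVA would use baseline in a change score or as a repeated level. Nor does the text say that the outcome's own baseline is what separates the two models. The supportable statement is that baseline is not fixed as a covariate.
- **That the secondary ANOVA averages the baseline visit into the comparison of arms.** The between-factors test is specified for the primary outcomes only. The secondary sentence does not name it, so nothing here relies on it.
- **That the secondary tests run above 5%.** This needs both models to be fitted and the more favourable one reported. The document does not say so. If the model is fixed without sight of the results, each test keeps its nominal level.
- **That omitting the minimisation factors certainly widens the standard errors.** This holds only if those factors predict the outcome in question, which the document does not show. No size is claimed for it.

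The 0.5 correlation is also a planning value for the primary analysis, so the loss for a given secondary scale may be smaller or larger, as the table shows.

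**Conclusion.** The concern holds in a limited form. The loss of precision is conditional: it arises only where ANOVA of a follow-up or change score is used, or where an ANCOVA omits the outcome's own baseline. Under those conditions the 1.33-fold variance means that about a third more patients would be needed for the same precision at one follow-up, or half as many again for the mean of both. The result assumes ρ = 0.5 and equal variances; the power figures also assume an effect of 0.5 SD and 1:1 allocation. Scope for choosing a model by result is real in the wording, but its use is not stated. Because only secondary outcomes are involved, neither the target of 70 nor the definition of efficacy changes. This is a worthwhile and inexpensive improvement, not a flaw that threatens the trial.

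**What to change.** In section 2.7, replace the choice between ANOVA and ANCOVA with one prespecified model for all continuous secondary outcomes: follow-up score on arm, adjusted for that outcome's own baseline score, sex, type of epilepsy and seizure control. Read the arm effect at the 4-week follow-up, and report the 16-week follow-up as the maintenance estimate. A mixed model over both follow-ups with the same covariates is acceptable, provided that it includes visit and arm-by-visit terms, so that each follow-up has its own arm effect.

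The cost is one sentence of wording. The baseline scores and the minimisation factors are already part of the planned data, so no visit, instrument or patient is added. The only downside is a few degrees of freedom for the covariates, which is negligible.
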